**Fig. 2 Fig2:**
[figure not shown]
Aerial map of Ratchasuda College (RC) at Mahidol University. A route between two on-campus locations is delineated

#### Aim 2

We will recruit a cohort of twenty BLV students currently enrolled in classes at Mahidol University. Students will be asked to don a wearable (bookbag) during all tasks requiring navigation for one week (10 days)**.** Ethograms will be constructed by coding the basic behaviors documented while navigating particular sections of campus, including public transport access points, street crossings, street hazards, e.g., areas with scaffolding, navigation to and through entrances, straight paths (to assess veering), curved paths, and elevation changes, e.g., stairs and ramps. We will collect data on the behavioral components of each situation to understand the effects of the environment on the participant as one moves through campus and the variables that trigger and modify related behaviors [27]. We will describe the mobility phenotype as BLV users interact with a complex range of obstacles in the various areas of campus, cataloging the vastly different reactions and consequences triggered by each. Particular obstacles and campus areas may have a higher likelihood of precipitating mechanical falls, leading to potentially catastrophic injuries. Thus, this process will guide the training of machine learning algorithms based on the specific task to be completed. For example, an intersection crossing near a bus stop for someone with a high degree of veering is particularly precarious; this and other related findings require specific attention and additional safety prompting. We will test navigation assistance (short-term) by comparing the initial five days with the VIS^4^ION system worn in passive mode (acquiring data, providing no assistance/feedback on location and orientation) to the final 5 days with the system worn in active or assistive mode (acquiring data and simultaneously providing assistance/audio feedback).

#### Aim 3

We will ask the same cohort of BLV students enrolled in Aim 2 to participate in focus group discussions (FGD) to assess the acceptability and appropriateness of VIS^4^ION. A research team member will conduct FGDs, each of which will consist of 6**–**8 individuals, and an interpreter will help facilitate the discussion [28].

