**Table Tabb:** 

Aims	Aim 1	Aim 2	Aim 3	Aim 4	Aim 5
Tasks	1) Multiple correlation of actual to inferred 3D position (goodness of fit metric comparing the actual and inferred 3D positions) 2) Average error as a function of distance from the center of the 3D map (mapping precision will likely vary as a function of position within the mapped region). The precision metric compares performance consistency to the ideal) 3) Positioning (xy) accuracy and viewing angle accuracy (comparing actual performance to the ideal, i.e., accuracy, shows the size and direction of biases in performance) 4) Beta localization	1) Average changes in normalized path length and variability in path length (i.e., percent change in path length and path variance; comparisons of pre/post path length indicate a potential change in confidence and ability in following a path without getting lost) 2) Average changes in normalized traversal time (i.e., percent change in time; comparison of pre/post traversal times indicates potentially improved general mobility and navigation) 3) For destinations that denote social activities, compute mean difference in time spent on such activities pre to post (comparisons between pre/post means indicate potential changes in levels of social interaction) 4) Pre vs. post fall rates (a comparison to determine if fall rates increase/decrease) 5) Assess QoL using the VFQ25 and WHO-QOLBREF 6) Assess physical function and mobility using IPAQ	Measure acceptability, feasibility, and appropriateness as lumped average scores (5-point Likert scale) across post-interview questionnaire and focus-group discussions	1) Average changes in normalized path length (i.e., percent change in path length) 2) Average changes in normalized traversal time (i.e., percent change in time) 3) For destinations that denote social activities, compute mean difference in time spent on such activities pre-to-post 4) Measure overall activity using total path length/day and total travel time/day 5) Measure BP and BMI pre-topost, and correlate with measures 1–4 6) Pre vs. post fall rates 7) Assess QoL using the VFQ25 and WHO-QOLBREF 8) Assess physical function and mobility using IPAQ 9) We will also conduct a process evaluation according to the Saunders Framework	1) Multiple correlation of actual to inferred 3D position (goodness of fit metric) 2) Average error as a function of distance from the center of the 3D map (mapping precision will likely vary as a function of position within the mapped region) 3) Compare (*t*-test) correlations and (linear model) average error functions between Aims 1 and 5 to show generalizability

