We will perform a content analysis of the transcripts and notes using NVIVO software [36]. Specific quotations, group interactions, and observations will be assigned codes based on content. The following are the core acceptability and appropriateness outcomes that will be assessed: (a) satisfaction or agreeability with the refined intervention design; (b) perceptions on how the intervention can be adopted within their setting; (c) perceived willingness or interest to participate; and d) perceived relevance and fit of the intervention for the setting. Significant inductive (emerging) codes will also be identified, assessing for differences by sex. Coded items will be grouped into a hierarchical, branching structure in which broad concepts are first identified. The themes and interpretive ideas emerging from those constructs are labeled using constant comparison techniques and subsequently synthesized using matrices structured by the main themes of the analysis [39, 40]. In addition, we will measure acceptability, feasibility, and appropriateness as lumped average scores (5-point Likert scale) across a 27-question post-interview questionnaire. Averages of > 2.5 will indicate an overall positive rating on each dimension, although low average scores on individual questions within each dimension (i.e., non-lumped) will be used to aid product development.

#### Aim 4

We will evaluate the effectiveness of our approach to increase efficient mobility among BLV students, as well as health and well-being. Descriptive statistics will be generated for quantitative data, and thematic content analysis will be performed for qualitative data. We will perform a content analysis of the transcripts and notes using NVIVO software [36], in a manner similar to what has been described above in Aim 3. Results will be categorized according to the seven dimensions of the Saunders Framework: fidelity, dose delivered, dose received (exposure), dose received (satisfaction), recruitment, reach, and context. Formative data will be reported iteratively to the study team throughout the trial, in order to improve intervention delivery, while summary data will be reported at the end of the trial along with the results of the trial. We will compare pre/post-differences in subjective assessments and in navigation and health metrics.

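### If the Aim 3 items are scored 1 to 5, the 2.5 cut-off for a positive rating lies below the neutral point of 3, so mildly negative averages would be reported as positive

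*Protocol article*

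**What the plan says.** In the protocol article, Statistical methods {20a}, Aim 3, the quantitative part of the plan reads "we will measure acceptability, feasibility, and appropriateness as lumped average scores (5-point Likert scale) across a 27-question post-interview questionnaire". The decision rule follows directly: averages above "2.5 will indicate an overall positive rating on each dimension". The same sentence adds that "low average scores on individual questions within each dimension (i.e., non-lumped) will be used to aid product development", which shows that higher scores are meant to be better.

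The Outcomes {12} table repeats the scale for Aim 3, "Measure acceptability, feasibility, and appropriateness as lumped average scores (5-point Likert scale) across post-interview questionnaire and focus-group discussions", without a cut-off. Neither place gives the numeric codes, the response anchors, a neutral value or a reason for choosing 2.5.

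The respondents are the Aim 2 cohort (Intervention description {11a}, Aim 3: "We will ask the same cohort of BLV students enrolled in Aim 2 to participate in focus group discussions"), which Trial design {8} sets at 20 students.

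**The concern.** The rule calls a dimension positive once its average passes 2.5. On a five-option item scored 1 to 5, the middle option is 3, and 2.5 falls between the second option and the middle one. The figure equals half of 5, which is not the midpoint of a scale that starts at 1. A group whose answers lean modestly towards disagreement could then be reported as finding the device acceptable, feasible or appropriate.

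At stake is the published Aim 3 conclusion. The three constructs are named in the abstract and in Objectives {7}, and they are the only metrics listed for Aim 3 in the Outcomes table. The 2.5 cut-off is the only numerical standard the article gives for them. This is a number the article states, so it is not a detail left to a fuller document.

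**Working it through.** **Inputs.** From the article: a five-point scale, a cut-off of more than 2.5 per dimension, higher scores better, 20 respondents. Assumed, because the article does not say: the item codes, and that the middle option is neutral.

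**Step 1. Where 2.5 sits under each coding.** Midpoint = (lowest code + highest code)/2. Position of the cut-off = (2.5 − lowest)/(highest − lowest).

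| Coding | Options | Midpoint | Position of 2.5 in the range |
|---|---|---|---|
| 1 to 5 | 5 | (1 + 5)/2 = 3.0 | 1.5/4 = 37.5%, below neutral |
| 0 to 4 | 5 | (0 + 4)/2 = 2.0 | 2.5/4 = 62.5%, above neutral |
| 0 to 5 | 6 | (0 + 5)/2 = 2.5 | 2.5/5 = 50%, at the midpoint |

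The value 2.5 is the midpoint only of a 0 to 5 scale, which has six options and so does not match the stated five-point scale. Reverse scoring is excluded because low item scores are the ones to be acted on.

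**Step 2. Width of the mislabelled band under 1 to 5 coding.** The band runs from just above 2.5 to just below 3.0. Its share of the range is (3.0 − 2.5)/(5 − 1) = 0.5/4 = 1/8.

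**Step 3. What an average in that band can look like (invented distributions, 1 to 5 coding).**
- 55% score 2, 30% score 3, 15% score 4: 0.55 × 2 + 0.30 × 3 + 0.15 × 4 = 1.10 + 0.90 + 0.60 = 2.60. This is labelled positive with 55% disagreeing and 15% agreeing.
- 74% score 2, 26% score 4: 0.74 × 2 + 0.26 × 4 = 1.48 + 1.04 = 2.52. This is labelled positive with nearly three in four disagreeing.

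**Step 4. How often a mildly negative cohort would be labelled positive (illustration only).** Take a true dimension mean of 2.75 on 1 to 5 coding, n = 20, and a participant-level SD of 0.5 to 1.0. The mean and the SD are both assumptions. With a normal approximation, P(observed mean > c) = 1 − Φ((c − 2.75)/(SD/√20)).

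| SD | SD/√20 | P(mean > 2.5) | P(mean > 3.0) |
|---|---|---|---|
| 0.5 | 0.112 | 0.987 | 0.013 |
| 0.8 | 0.179 | 0.919 | 0.081 |
| 1.0 | 0.224 | 0.868 | 0.132 |

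Such a cohort would be called positive 87% to 99% of the time at 2.5, against 1% to 13% of the time at 3.0.

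**The case against.** The strongest reply is that the coding is assumed. The article says only that the scale has five points. The questionnaire is not shown, and a journal article may leave item codes to a fuller document. Under 0 to 4 coding 2.5 lies above the neutral value of 2.0, and a cut-off above neutral is a reasonable definition of positive. The plan never claims that 2.5 is the neutral value. This stands, and it makes the point conditional. Nothing in the article indicates 0 to 4 coding, however, and 1 to 5 is the usual convention.

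The second reply concerns consequence. A reader might infer that 2.5 is a success threshold that decides whether the device is adapted or whether the randomised phase goes ahead. The documents do not support that. The article calls the result an overall rating and attaches no hypothesis test or go/no-go decision to it, and Participant timeline {13} schedules Aim 4 without reference to it. Product development is tied to low scores on individual questions, in the same sentence as the cut-off, and Trial design {8}, Aim 3, draws improvements from interviews and surveys generally. The content analysis of the focus groups does not use the cut-off at all. A dimension averaging 2.7 would still have its weak items examined. This reply also stands and limits the severity. It does not correct the dimension-level label, which would still be reported.

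Third, a reader might infer that any cohort leaning negative would be called positive. Under 1 to 5 coding, dimensions averaging 2.5 or less are correctly not called positive. Only the band between 2.5 and 3.0 is affected, and nothing in the article suggests that averages will fall there.

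**Conclusion.** The point holds on the assumption that items are scored 1 to 5 with a neutral middle option. Dimension means above 2.5 and below 3.0, one eighth of the range, would then be reported as positive although they lean negative, and no other section of the article corrects this. If items are scored 0 to 4, no negative average is mislabelled and what remains is to state the coding.

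The damage is to the wording of the Aim 3 conclusion on acceptability, feasibility and appropriateness. No randomised comparison, sample size or safety decision depends on the number. Severity is minor to moderate.

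**What to change.** State the item codes and response anchors in the Aim 3 statistical methods, and define a positive rating as a dimension mean above the scale's neutral point: above 3.0 if items are scored 1 to 5. If the instrument is scored 0 to 4, say so; 2.5 can then stand with a one-line justification. A 95% confidence interval for each dimension mean across the 20 participants would be a useful optional addition.

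The cost is one number and one clause. Trial status says that enrolment had not begun, and neither the design, the sample size nor the data collection changes. The downside is a slightly stricter criterion: under 1 to 5 coding, means above 2.5 and up to 3.0 would no longer earn the positive label.

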### Methods for additional analyses (e.g., subgroup analyses) {20b}

Post hoc analyses will be treated as exploratory hypothesis testing and labeled as such in any written reports. Such analyses will allow us to explore additional potential connections found within our data, and plan for future studies to formally test such hypotheses. No post hoc analysis will be used to form the basis for general conclusions or recommendations issued from these studies.

### Methods in analysis to handle protocol non-adherence and any statistical methods to handle missing data {20c}

Missing data are expected to be distributed according to MAR [41]. If the rate of missing data (r) is not related to the multivariate output (y) after taking account of x (inputs):

## $$P\left(r_i=0\vert{\mathcal x}_{i,}{\mathcal Y}_{mis,\mathfrak i;}\phi\right)=P\left(r_i=0\vert{\mathcal x}_i,;\phi\right),$$

Then the missing data are ignorable. However, if instead, this simplification is not valid, such that NMAR holds, then the data are not ignorable, and a Bayesian multiple imputation technique based on the prior predictive distribution (Hudson, 2021) or a sampling-based technique for generating samples of data (McElreath, 2016) meeting the characteristics of the missing data will be used to account for missing data.

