Each FGD session will last roughly 60 min and include participants’ perceptions and experiences while navigating the VIS^4^ION system. The FGDs will be guided by pre-determined questions related to general perceptions of the VIS^4^ION system, as well as thoughts on the facilitators and barriers of the intervention. The FGD sessions will be audio-recorded verbatim and later transcribed and translated into English by the research team. During the sessions, the research team member will also take field notes.

#### Aim 4

A cohort of 20 (new) participants will be recruited to assess extended-use benefits over one month. We will create two groups for the randomized crossover design. Each participant will be randomized to either sequence A (10 participants) or sequence B (10 participants). During the first 15 days, group A will go through an active phase and then a passive phase for the next 15 days. Reciprocally, group B will go through a passive phase for the first 15 days and then an active phase for the second half of the month. During the passive phase, the wearable will be maintained in a monitoring mode and simply acquire data, providing no assistance/feedback on location and orientation. During the active phase, the wearable will have an activated assistive mode, i.e., the wearable will acquire data and simultaneously provide assistance/audio feedback. We will evaluate the effectiveness of the wearable for increasing navigation and quality of life. We hypothesize that the VIS^4^ION wearable will improve navigation and quality of life in individuals with visual disabilities.

During the active phase, subjects will complete their daily activities while wearing VIS^4^ION and using the mapping and localization microservice to facilitate wayfinding. Throughout the study we will monitor navigation performance through the same metrics as delineated in Aim 2 [week 2 compared to week 4], as well as to monitor for any falls that may occur (IMU-based alerting); we will also subjectively assess visual function through the 25-Item National Eye Institute Visual Function Questionnaire (VFQ25) [29], physical function and mobility, through the International Physical Activity Questionnaire (IPAQ) [30, 31], and QoL, through the World Health Organization QoL Brief (WHO-QoL-BREF) [32, 33]. The subjective assessments will be performed on day 0 (day of device delivery and initiation) and on the final day of the trial (day 31).

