### Sample size [1]

A total of 40 visually impaired subjects will be recruited over the 5 years of this proposed research program. In the first phase, we will focus on demonstrating that travel has improved, using a metric based on the ratio of path length. Path length is a non-normal variate, right-skewed, and must be transformed to satisfy the constraints of a parametric statistical test.

We use log-transformed path-length ratios for the power calculation, by which we determined that, with a statistical power of at least 0.8, we will be able to detect a path-length difference for 20 subjects in which the initial path lengths are 40% shorter than those taken when using the navigation aid, assuming a standard deviation of length-ratios no larger than 2.5.

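### For data judged not missing at random, the plan permits imputation from the prior predictive distribution, and its ignorability condition omits observed outcomes, so some MAR dropout could be sent there

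*Protocol article*

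**What the plan says.** Section {20c} starts from a default: "Missing data are expected to be distributed according to MAR". It then says when missingness may be ignored, namely when it "is not related to the multivariate output (y) after taking account of x (inputs"). The equation that follows has the same content: the probability of being missing given x and the missing outcomes must equal the probability given x alone. Observed outcomes appear on neither side.

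The next sentence sets the consequence of failure: "if instead, this simplification is not valid, such that NMAR holds, then the data are not ignorable". Two methods are then offered for that case. The first is "a Bayesian multiple imputation technique based on the prior predictive distribution". The second is introduced by "or a sampling-based technique for generating samples of data" and is meant to produce data that share the characteristics of the missing data. No rule chooses between the two, and no prior is stated.

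The setting that matters is Aim 4 (Intervention description {11a}): a two-period crossover of 20 participants, 15 days per period and 10 per sequence, with navigation recorded throughout. The questionnaires are completed only on day 0 and day 31.

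**The concern.** There are two faults, and they compound.

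**The distribution.** The prior predictive distribution is what the model expects before any data are seen. Imputing from it ignores the other participants' outcomes and the participant's own recordings from the other period. Multiple imputation ordinarily draws from the posterior predictive distribution given the observed data. Nor is the prior predictive an NMAR model by itself, because it contains no statement of how the missing values depart from the observed ones.

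**The trigger.** The printed condition is covariate-dependent missingness, which is stricter than MAR. MAR lets missingness depend on observed outcomes. A participant who leaves in period two because of a recorded period-one result can be MAR, yet fails the printed condition. The section equates that failure with NMAR, so an ignorable pattern could be handed to a method that discards the data that make it ignorable. Whether the condition holds also turns on unobserved values, so the data cannot settle which branch applies.

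At stake is an Aim 4 navigation estimate pulled toward whatever prior is chosen.

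**Working it through.** Section {20c} states no figure to reproduce. The check has three steps.

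**1. Printed condition against MAR.** Let r = 0 denote a missing value.

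- MAR: P(r=0 | x, y_obs, y_mis) = P(r=0 | x, y_obs).
- Printed: P(r=0 | x, y_mis) = P(r=0 | x).

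Under MAR, the left side of the printed equation is the average of P(r=0 | x, y_obs) over the distribution of y_obs given x and y_mis. If dropout depends on y_obs, and y_obs is correlated with y_mis, that average generally changes with y_mis and the printed equality fails.

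A simulation of 2,000,000 records shows this. Dropout depended only on the earlier observed outcome (logit p = -1.6 + y_obs; correlation with the later outcome assumed):

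| Correlation | Overall missing | P(missing), lowest quartile of y_mis | P(missing), highest quartile |
|---|---|---|---|
| 0.3 | 0.207 | 0.155 | 0.264 |
| 0.5 | 0.207 | 0.124 | 0.305 |
| 0.7 | 0.206 | 0.095 | 0.346 |

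By construction, missingness here does not depend on y_mis once y_obs is fixed. It is MAR in every row, and the printed condition fails in every row.

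**2. What prior-predictive draws can do.** Inputs: n = 20 (Aim 4); m missing values (assumed 2, 4, 6, since no dropout rate is given); true mean log ratio 0 (assumed); prior centred on ln(0.6) = -0.511. That centre is borrowed only as a scale from the Sample size section, where "the initial path lengths are 40% shorter than those taken when using the navigation aid". The expected shift in the mean is (m/20) × ln(0.6), and the apparent change in the ratio is 1 - exp(shift).

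- m = 2: 0.10 × -0.511 = -0.051, a change of 5.0%.
- m = 4: 0.20 × -0.511 = -0.102, a change of 9.7%.
- m = 6: 0.30 × -0.511 = -0.153, a change of 14.2%.

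**3. Prior against posterior predictive under MAR.** Assumptions: n = 20; true mean log ratio -0.511; log SD ln(2.5) = 0.916, reading the 2.5 in the Sample size section as a geometric SD; correlation 0.6 with the earlier outcome; dropout depending on that outcome; 1,500 runs; 20 imputations; prior SD 1. Each cell gives the estimated mean, with the full-data mean of the same runs in brackets.

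| Missing | Prior predictive, centre -1.02 | Prior predictive, centre 0 |
|---|---|---|
| 10% | -0.614 (-0.522) | -0.506 (-0.514) |
| 20% | -0.693 (-0.514) | -0.485 (-0.511) |
| 30% | -0.765 (-0.511) | -0.454 (-0.514) |

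The shifts are -0.09, -0.18 and -0.25 with the first prior, and +0.01, +0.03 and +0.06 with the second. Posterior-predictive imputation, using y_obs, stayed within 0.003 of the full-data mean in all these runs (for example -0.508 against -0.511 at 20%).

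The small shifts in the last column are a coincidence of the set-up. At 20% missing, +0.026/0.197 = 0.13, so the missing values averaged about -0.13, which happens to lie near the prior centre of 0.

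**The case against.** Several points on the other side stand.

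- **It is one option of two.** A reader might infer that the plan fills all missing outcomes from the prior. It does not: the sampling-based alternative need not draw from the prior, and the branch is a contingency behind a MAR default.
- **The branch also says that NMAR holds.** One could argue that MAR dropout would never enter it. But the sentence treats failure of the condition as NMAR, so a literal reader would send it there. This would be cured if x were meant to include earlier outcomes, which the contrast between inputs and output does not suggest. A stray comma after x in the equation leaves room for a lost term, but the words beside it also name only x.
- **Scope is narrow.** With questionnaires only on day 0 and day 31, there is no first-period score to drive dropout, and day 0 can serve as an input. The trigger fault concerns mainly the continuously recorded navigation data.
- **A prior could carry an NMAR shift.** Under NMAR the departure must come from assumption, and a prior built for the missing group could supply it. No such prior is stated, and the cited source is not available here. Detail of that kind may sit in a statistical analysis plan; the named method and the printed condition would still need correcting.
- **Power.** A reader might infer a severe loss of power. The documents do not support a figure: any result depends on an unstated prior and an assumed log SD, and Aim 4 is described as exploratory, with Bayesian model comparison for its pre-post metrics.
- **Likelihood.** The article gives no dropout rate or reasons, so it cannot be said how often this branch would be used.

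**Conclusion.** The point holds as a fault in what section {20c} states. It permits an imputation distribution that uses none of the observed trial data, with no rule for choosing it over the alternative, and it prints an ignorability condition stricter than MAR. In the Aim 4 crossover, dropout driven by an observed first-period navigation result would be labelled NMAR and could be imputed from the prior.

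The size cannot be fixed from the document. It ranges from almost nothing, when the prior centre happens to match the missing values, to an apparent change of 5.0% to 14.2% from no true effect, with 2 to 6 of 20 values missing and a prior centred on a 40% difference. These figures rest on assumed priors, dropout and, in the simulations, correlation. It does not follow that the trial's main analysis is compromised, because MAR is the expected case.

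**What to change.** In section {20c}:

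1. Write the ignorability condition as conditional on x and all observed y, from both periods where available.
2. Keep the MAR analysis as primary, so that the method is not chosen by a condition on unobserved values.
3. Replace the prior predictive distribution with the posterior predictive distribution given x and all observed y.
4. Address NMAR as a sensitivity analysis with an explicit departure from MAR, for example a stated range of delta shifts added to the posterior predictive draws, or a pattern-mixture model. Either drop the unspecified sampling-based alternative or say when it applies.

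The cost is a wording change in one section and a short extra sensitivity table. No new data or participants are needed.
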